### Multicenter quality assurance and data management plan

To ensure consistency across multiple centers and minimize heterogeneity, our research team implemented standardized procedures for assessment implementation, data collection, and quality control across all participating sites.

Unified Training and Standard Operating Procedures (SOPs): All investigators and research staff underwent centralized training before study initiation. This included detailed instructions on assessment implementation, data collection procedures, outcome assessment criteria and standardized delivery of multicomponent intervention recommendations across sites. Standardized assessment manuals and implementation checklists were distributed to each center, and regular online meetings were conducted to reinforce protocol adherence. A standardized case-report form (CRF) was developed and used uniformly across all sites to ensure consistent data recording.

Data Standardization and Quality Control: We established a multi-level data cleaning and quality control process. First, automated validation rules were embedded in the electronic data capture (EDC) system to check for completeness and logical consistency at the time of data entry. Second, centralized outlier detection and missing-data handling procedures were applied. Third, independent data verification was performed to ensure cross-field consistency and data integrity.

Centralized Data Management and Feedback Loop: A dedicated data management team was responsible for regular monitoring, data cleaning, and feedback to each participating center. Any discrepancies or missing data were promptly communicated to the sites for resolution, ensuring the reliability and completeness of the final dataset.

All procedures were conducted in accordance with the Guidelines for Data Management in Clinical Research, ensuring high-quality data to support subsequent modeling and analysis.

### Measurements

#### Primary outcome

Frailty status in elderly CKD patients is defined using the FRAIL scale (Fatigue, Resistance, Ambulation, Illness, and Weight Loss; total score ≥ 3 indicating frailty). The primary analytical objective is to examine associations between clinical and non-clinical indices and frailty status and to support the development of individualized frailty risk prediction models.

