### Recruitment and data collection

This is a multicenter, bidirectional cohort study. Eligible participants will be consecutively enrolled from nephrology and internal medicine departments across seven hospitals in Beijing. Retrospective data extraction will be performed only at the coordinating center (Beijing Chaoyang Hospital), while all participating centers will contribute prospective data collection. Pre-admission and admission-related baseline data, including demographic, clinical, and laboratory characteristics, will be retrospectively extracted from the electronic medical records (EMRs) at the coordinating center for eligible historical cases, while baseline standardized assessments will be prospectively performed at hospital admission for newly enrolled participants across all participating centers starting on January 3, 2025. During the prospective data collection phase, each participant will undergo standardized assessments encompassing: structured questionnaires for demographics, comorbidities, physical examinations and anthropometric measurements; laboratory tests including blood and urine biochemistry, inflammatory and metabolic indicators; geriatric assessment scales, frailty, cognition, nutrition, psychological state, physical performance. Collected variables were categorized into two groups: routinely available clinical indices (demographics, medical history, anthropometric measures and laboratory tests) and non-clinical indices, defined as non-routinely acquired geriatric assessment data (frailty scales and cognitive, functional, nutritional, and psychological assessments), which require specialized evaluation and are resource-intensive in routine clinical practice. All data will be entered into a harmonized electronic case-report form (eCRF). The database will be centrally curated at Beijing Chaoyang Hospital, following prespecified data quality control and harmonization procedures described below.

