### Knowledge-distillation-based model optimization

A teacher–student learning framework will be implemented. The teacher model is trained using full indices including both clinical and non-clinical indices. The student model, restricted to routinely available clinical indices only, is trained by minimizing the distillation loss between teacher and student outputs, enabling the student model to learn compressed representations capturing information patterns related to geriatric assessment and frailty evaluation from routinely available clinical data. This strategy allows simplified deployment of the prediction model in routine clinical environments with limited data availability.

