The expected outcomes include the development of an interpretable AI-assisted frailty prediction framework, establishment of a multicenter CKD–frailty database, and provision of quantitative decision-support outputs to assist individualized risk stratification and care planning. In clinical practice, the proposed framework is intended to support frailty risk stratification and individualized care planning rather than replace clinical judgment. Model-generated frailty risk scores and interpretable feature contributions may assist clinicians in identifying high-risk patients who could benefit from comprehensive geriatric assessment and targeted interventions, while facilitating routine monitoring of lower-risk individuals in primary care settings. At the population level, standardized risk outputs derived from multicenter data may contribute to evidence generation for defining frailty risk thresholds and stratified management pathways, thereby providing supportive data for future clinical pathway optimization and guideline refinement.

Several limitations should also be acknowledged. First, model performance may be influenced by temporal changes in patient characteristics and treatment patterns, potentially leading to model drift. To minimize this impact, continuous data updating and periodic model recalibration will be implemented within the bidirectional cohort framework. Second, although knowledge-distillation techniques enable prediction using laboratory-only inputs, the inferred representations of clinician-rated frailty and geriatric assessment information derived from laboratory features require further validation. This limitation will be addressed through prospective data collection and external validation across broader and more diverse patient populations. Third, residual heterogeneity across participating centers may persist due to variations in clinical practice patterns and healthcare infrastructure. This will be mitigated through standardized assessment and implementation protocols, centralized quality control procedures, and harmonized data management strategies implemented across all study sites.

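### FRAIL ≥ 3 contains an Illness item (and, by name, a Weight Loss item) while comorbidity and anthropometric variables serve as predictors, so their role as frailty determinants is partly definitional

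*Protocol article*

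**What the plan says.** - **Outcome.** The Primary outcome section defines frailty on five named items with a cut at 3: "Fatigue, Resistance, Ambulation, Illness, and Weight Loss; total score ≥ 3 indicating frailty". It gives no scoring rule for any item. It makes the association of clinical and non-clinical indices with this status the primary analytical objective.
- **Predictors.** Recruitment and data collection defines the "routinely available clinical indices (demographics, medical history, anthropometric measures and laboratory tests") group. Comorbidities are among the data that come from "structured questionnaires for demographics, comorbidities, physical examinations and anthropometric measurements".
- **Timing.** In the prospective part, "baseline standardized assessments will be prospectively performed at hospital admission for newly enrolled participants". Outcomes and analysis states that there are no follow-up endpoints, so predictors and outcome share one time point.
- **Student model.** Knowledge-distillation-based model optimization says: "The student model, restricted to routinely available clinical indices only". The limitations in the Discussion instead say that "knowledge-distillation techniques enable prediction using laboratory-only inputs".
- **Use of the results.** Outcomes and analysis plans causal learning to find what contributes to frailty. The Statistical plan adds causal-effect estimation, and Validation and evaluation adds SHAP attributions and causal-effect displays.

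**The concern.** A variable that helps to make up an outcome score is associated with that score even if it has no relation to anything else the score measures. The Illness item concerns disease burden, and medical history and comorbidities are offered as predictors at the same visit. The Weight Loss item concerns weight change, which could enter through anthropometrics if earlier weights are used.

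Two readings of the results are at stake:

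- Causal and SHAP outputs would rank comorbidity as a driver of frailty, and these outputs are meant to support individual intervention suggestions. Part of that ranking would follow from the outcome definition.
- A good student AUC would be taken as evidence that routine data reproduce what geriatric assessment measures. Part of it may reflect only the overlapping item or items.

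**Working it through.** **The plan's own figures.** Sample size justification gives 10 × 30 / 0.20 = 1,500 participants and 1,500 × 0.20 = 300 events. The precision is 1.96 × √(0.20 × 0.80 / 1,500) = 2.02 percentage points. Both reproduce, and neither is affected by this point.

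**Inputs for the illustration.** From the documents: five items, cut at 3, 20% frailty. Assumed: item prevalences, independence of items, and exact recovery of the item from the predictors. The last assumption makes every figure an upper bound.

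**Illness alone.** Let R be the sum of the other four items and p_I the Illness prevalence.
- P(Illness | frail) = p_I × P(R ≥ 2) / 0.20
- P(Illness | not frail) = p_I × [1 − P(R ≥ 2)] / 0.80
- AUC = 0.5 + (difference of the two) / 2

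With equal prevalences, P(score ≥ 3) = 0.20 requires p = 0.3266 for each item. Then P(R ≥ 2) = 0.3954 and P(R ≥ 3) = 0.1052.
- P(Illness | frail) = 0.3266 × 0.3954 / 0.20 = 0.646
- P(Illness | not frail) = 0.3266 × 0.6046 / 0.80 = 0.247
- AUC = 0.5 + (0.646 − 0.247) / 2 = 0.70
- Frailty risk is 39.5% with the Illness point and 10.5% without it, a ratio of 3.8. Here Illness is unrelated to the other four items by construction, so all of this is definitional.

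**Both items, same case.** Let S = Illness + Weight Loss.
- P(S = 0, 1, 2) = 0.4535, 0.4399, 0.1067
- P(frail | S) = 0.0348, 0.2503, 0.6946
- Distribution of S among the frail: 0.079, 0.551, 0.370; among the others: 0.547, 0.412, 0.041
- AUC = 0.079 × 0.547/2 + 0.551 × (0.547 + 0.412/2) + 0.370 × (0.547 + 0.412 + 0.041/2) = 0.80

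**Other assumed prevalences**, by the same enumeration, with the prevalence of the other three items solved to keep frailty at 20%:

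| Illness | Weight Loss | Other three, each | AUC, Illness alone | AUC, both | Frailty risk with / without Illness point | Ratio |
|---|---|---|---|---|---|---|
| 32.7% | 32.7% | 32.7% | 0.70 | 0.80 | 40% / 11% | 3.8 |
| 22.5% | 22.5% | 39.9% | 0.67 | 0.78 | 45% / 13% | 3.5 |
| 5% | 10% | 52% | 0.56 | 0.66 | 57% / 18% | 3.1 |
| 5% | 20% | 48% | 0.55 | 0.72 | 55% / 18% | 3.0 |
| 15% | 10% | 48% | 0.64 | 0.72 | 51% / 15% | 3.5 |
| 15% | 20% | 44% | 0.64 | 0.76 | 49% / 15% | 3.3 |
| 30% | 10% | 42% | 0.71 | 0.76 | 42% / 10% | 4.0 |
| 30% | 20% | 38% | 0.70 | 0.78 | 41% / 11% | 3.8 |

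Ratios are taken from unrounded risks. Against an outcome without the overlapping items, every AUC in this independent case is 0.50 and every ratio is 1.

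**Correlated items.** A simulation used a one-factor latent normal model, 400,000 draws, latent correlation 0.2 to 0.4, Illness at 5–30% and Weight Loss at 10–20%. Both items gave an AUC of 0.70 to 0.89 for FRAIL ≥ 3, and 0.55 to 0.72 for at least two of Fatigue, Resistance and Ambulation. Illness alone gave 0.58 to 0.80, and 0.52 to 0.67 for those three items. With correlation, some of the signal is genuine, and only an analysis on the reduced score separates the two parts.

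**The case against.** **For prediction this is not an error.** The student is meant to estimate FRAIL status from data that clinicians hold, and medical history is such data. Its AUC for FRAIL ≥ 3 is valid for that target. This stands. A reader might infer that the student's performance is invalid through leakage, and the documents do not support that. The point concerns interpretation.

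**Shared scoring is not stated.** A reader might infer that two of the five items are scored from the student's inputs. The article gives item names only, so overlap of content is all that can be claimed. For Illness that overlap is plain. For Weight Loss it is conditional: the item is a change over time, and no earlier weight or weight change is listed as a predictor. The pre-admission data extracted at the coordinating center are not said to include weight.

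**The figures rest on assumptions.** They do, and the 0.50 comparison follows directly from independence. With correlated items, Illness and Weight Loss do carry information on the other three, so it would be wrong to say they carry none. The student also has demographics and laboratory tests.

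**Part of this may sit in a fuller plan, and the Discussion tempers it.** The candidate predictors are not listed in the article, and the limitations say that inferred geriatric information needs further validation. That softens the AUC reading. It does not address the determinant analyses, whose outcome, predictor classes and causal purpose the article itself fixes.

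**The laboratory-only phrase is a slip.** Probably so: elsewhere the Discussion gives the student laboratory and clinical variables. It adds little by itself, but it bears on whether the overlap exists.

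**Conclusion.** The concern holds for the association, causal and SHAP results. As written, comorbidity burden is analysed as a cause of a score that includes an Illness item, at the same time point, with no separation of the two. Weight change joins it only if earlier weights enter the predictors. The student's AUC stands as prediction of FRAIL ≥ 3, but alone it is not evidence of independent geriatric information.

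The size cannot be derived from the documents. Under independent items and exact recovery, the upper bounds are an AUC of about 0.55 to 0.71 for Illness alone and 0.66 to 0.80 for both, over the assumed prevalences. These should not be read as the share of the student's eventual AUC that is artefact. The target of 1,500 is unaffected.

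A related but separate matter is that the non-clinical indices include "frailty scales and cognitive, functional, nutritional, and psychological assessments", and "The teacher model is trained using full indices including both clinical and non-clinical indices". The text does not say whether FRAIL itself is withheld from the teacher. Withholding it would not remove the overlap described here.

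**What to change.** 1. **Primary outcome, Outcomes and analysis, Statistical plan.** For the association, causal-effect and SHAP outputs, report comorbidity variables against a FRAIL score without the Illness item, and any weight-change variable against a score without the Weight Loss item. Show each beside the full-score result and interpret it as a determinant only on the reduced score. Fix the form of the reduced score in advance, for example as a count, so that no cut is chosen after seeing the data. Comorbidity and weight need not be barred from the reports.
2. **Validation and evaluation.** Add, as a sensitivity analysis, the student's AUC for the Fatigue-Resistance-Ambulation subscore, with its cut stated in advance. The primary outcome and the deployed model stay as they are.
3. **Discussion.** Make the laboratory-only description agree with the student's inputs in Recruitment and data collection, the Fig. 2 caption and the distillation section.

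The cost is a few extra model fits and some wording, with no further participants. It assumes that item-level FRAIL responses are recorded, which the article does not state. For historical cases it lists only demographic, clinical and laboratory data. The determinants and the AUC may read less favourably.

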#### Secondary outcomes

Secondary outcomes comprise multidomain geriatric indicators related to frailty and intervention guidance: Cognitive function: Mini-Mental State Examination (MMSE) or Montreal Cognitive Assessment (MoCA); Nutritional status: Mini Nutritional Assessment–Short Form (MNA-SF); Psychological status: anxiety and depression; Comprehensive Geriatric Assessment (CGA) including physical performance (gait speed, grip strength, chair-stand test), functional ability (ADL, IADL).

Variable definitions will follow KDIGO 2024 and AWGS 2019 guidelines to ensure inter-center comparability. The integrated dataset will be used to identify older CKD patients at high risk for frailty and to generate individualized decision-support recommendations for nutritional, psychological, and physical-activity interventions through interpretable AI models.

### Model development and validation

An overview of the proposed AI modeling framework, including causal learning, knowledge distillation, and clinical deployment workflow, is illustrated in Fig. 2.

**Fig. 2 Fig2:**
[figure not shown]
Overview of the proposed causal-learning and knowledge-distillation framework for frailty risk prediction and individualized intervention in elderly patients with CKD. Clinical indices represent routinely available clinical variables (demographics, medical history, anthropometric measures and laboratory tests), while non-clinical indices represent resource-intensive geriatric assessment data (frailty, cognitive, functional, nutritional, and psychological assessments). The full-indices model is trained using both clinical and non-clinical indices, whereas the clinical-indices-only model is optimized through knowledge distillation to enable frailty risk prediction and intervention decision support in data-limited clinical settings

### Causal-learning-based frailty modeling

Patient-level clinical indices and non-clinical indices will first be processed using a structured modeling pipeline, as illustrated in Fig. 2. Raw input variables will be transformed into standardized feature representations through the patient information encoding module. These encoded features will then be input into the disease feature factorization module to generate latent disease-related feature factors. The extracted feature factors will subsequently be used for causal structure estimation.

Based on the learned feature relationships, a causal mask will be constructed to represent the dependency constraints among variables. This causal mask will be integrated into the downstream prediction network to guide feature interaction and information flow during model inference. Finally, the masked feature representations will be used as inputs to the prediction module to generate frailty risk estimates and intervention decision-support outputs for elderly patients with CKD.

### Knowledge-distillation-based model optimization

A teacher–student learning framework will be implemented. The teacher model is trained using full indices including both clinical and non-clinical indices. The student model, restricted to routinely available clinical indices only, is trained by minimizing the distillation loss between teacher and student outputs, enabling the student model to learn compressed representations capturing information patterns related to geriatric assessment and frailty evaluation from routinely available clinical data. This strategy allows simplified deployment of the prediction model in routine clinical environments with limited data availability.

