### Clinical workflow integration and deployment pathway

After model training and validation, the optimized student model will be integrated into an electronic medical record (EMR)–linked clinical decision-support interface. Routinely available clinical indices will be automatically extracted as model inputs. The system will generate individualized frailty risk scores and intervention suggestions, which will be presented to nephrologists and geriatricians through a structured dashboard. Model outputs will serve as assistive decision-support information, while final clinical decisions will remain under physician supervision, ensuring a human-in-the-loop implementation strategy.

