### Validation and evaluation

Internal validation, 70% of data used for model training and 30% for testing within the Chaoyang Hospital dataset. External validation, independent testing using data from six partner centers. Performance metrics, AUC, calibration curve, Brier score, and decision-curve analysis. Model explainability, assessed using SHAP-based feature attribution and causal-effect visualization to ensure interpretability and clinical credibility.

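### The causal structure is learned from clinical plus geriatric indices, but the deployed student sees clinical indices only, and no stated step supports reading its attributions or suggestions causally

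*Protocol article*

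**What the plan says.** All references are to the Methods of the protocol article.

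- **Causal-learning-based frailty modeling.** Both index sets enter the causal pipeline: "Patient-level clinical indices and non-clinical indices will first be processed using a structured modeling pipeline". They are reduced to latent factors, and "The extracted feature factors will subsequently be used for causal structure estimation". On the mask built from this, the article says: "This causal mask will be integrated into the downstream prediction network to guide feature interaction and information flow during model inference". The section closes with the step that produces the results, where "the masked feature representations will be used as inputs to the prediction module to generate frailty risk estimates and intervention decision-support outputs".
- **Knowledge-distillation-based model optimization.** "The teacher model is trained using full indices including both clinical and non-clinical indices". The student has the clinical indices alone and "is trained by minimizing the distillation loss between teacher and student outputs". The section says that this lets the student pick up, from routine data, patterns that belong to the geriatric assessment.
- **Clinical workflow integration and deployment pathway.** The student is the model that goes into the record system. "Routinely available clinical indices will be automatically extracted as model inputs", and the system returns risk scores and intervention suggestions.
- **Validation and evaluation.** "Model explainability, assessed using SHAP-based feature attribution and causal-effect visualization to ensure interpretability and clinical credibility". No model is named. The performance metrics are AUC, calibration curve, Brier score and decision-curve analysis.
- **Statistical plan.** Do-calculus, counterfactual simulation and feature-importance mapping are to yield causal effects. Neither a model nor a variable set is named.

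**The concern.** The claim to causal interpretability rests on a structure estimated with the geriatric indices present. The model that clinicians will use does not have those indices, and its one stated link to the teacher is agreement of outputs. Agreement of outputs transfers predicted risk. It does not transfer the constraint that a given marker has no effect of its own.

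The student is also meant to recover geriatric information from routine variables, so using proxies is its purpose. That is sound for prediction. It becomes a problem if a proxy's weight is displayed as a causal contribution, or if a suggestion is built on what the model predicts when the proxy is changed. A laboratory value that only tracks nutritional or functional status could then look like a target for action.

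**Working it through.** **1. The sections side by side**

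| Element | Full-index model (teacher) | Student |
|---|---|---|
| Inputs | clinical and geriatric | clinical only |
| Latent factors and mask | estimated from both index sets | not stated |
| Training link | not at issue here | loss between outputs |
| Deployed | no | yes |
| Issues suggestions | yes, if it is the masked prediction module | yes, through the deployed system |
| SHAP and causal-effect display | model not named | model not named |
| Do-calculus, counterfactuals | model not named | model not named |

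The causal structure has no stated path from the middle column to the right-hand one. The article's sample-size figures play no part in this point.

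**2. The possible readings of the student**

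- *No mask.* Nothing stops weight from falling on proxies.
- *The teacher's mask restricted to clinical indices.* If it blocks markers that merely track geriatric status, it works against the student's stated purpose. If it lets them through, they carry proxy weight.
- *A mask learned afresh from clinical indices.* Geriatric factors that affect both a marker and frailty are now unmeasured common causes. The clinical data alone cannot in general tell a proxy from a cause.

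**3. Illustration with an unmasked student (all inputs assumed)**

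Let Z be a standard normal geriatric factor, with teacher risk = expit(−1.75 + Z), so that mean risk is 18.6%. A laboratory marker L = rZ + √(1 − r²)·e, where e is standard normal noise, has no effect on frailty. The teacher gives it zero weight. The student is a logistic model in L fitted to the teacher's risks.

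| r | Student OR per SD of L | Predicted risk at the mean of L | Predicted risk at +1 SD | AUC of L for frailty |
|---|---|---|---|---|
| 0.3 | 1.30 | 18.3% | 22.6% | 0.57 |
| 0.5 | 1.57 | 17.7% | 25.2% | 0.62 |
| 0.7 | 1.91 | 16.8% | 27.9% | 0.67 |

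At r = 0.5, moving L from +1 SD to its mean appears to cut risk by 25.2 − 17.7 = 7.5 percentage points. The true change is nil. The AUC rises above 0.50 because of the proxy, so the planned metrics reward it.

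**4. Illustration with a masked student (linear, all inputs assumed)**

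Teacher logit = −1.5 + bG + 0.5·C2. G is the geriatric factor, C1 = 0.8G + 0.6e is a non-causal marker, C2 is a true cause independent of G, and all have unit variance.

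- Without a mask, the student's weight on C1 is 0.8b, which is 0.40, 0.80 and 1.20 for b = 0.5, 1.0 and 1.5. C2 stays at about 0.50.
- With a mask that excludes C1, C1 carries nothing and C2 is still about 0.50. A correct mask in the student can therefore preserve the structure in this case.
- That good result depends on C2 being independent of G. If G also affects C2, with correlation ρ, the masked student's weight on C2 is 0.5 + bρ. With b = 1.0 this is 0.5 + 0.3 = 0.80 at ρ = 0.3, and 0.5 + 0.5 = 1.00 at ρ = 0.5, against a true 0.50. The mask removes the excluded proxy but not the confounding of the variables it keeps.

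**The case against.** **The student may have a mask.** A reader might infer that the causal layer stops at the teacher and that the deployed tool has no causal basis at all. The documents do not support that. The network in which the mask acts is not identified as teacher or student, an output loss is compatible with a masked student, and Fig. 2, which is cited for how the parts connect, is not available here. This part of the objection stands. What remains is that no route is stated, and that neither possible mask would by itself justify a causal reading.

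**The causal outputs are not tied to the student.** This is correct. The explainability sentence and the Statistical plan name no model, and a counterfactual run on the student is nowhere specified. But the student-based system issues the suggestions, and the article does not say whether these come from separate full-index estimates or from the student's own attributions.

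**The simulation assumes its result and is not about distillation.** This also stands. The simulated student has one input and no mask, and fitting the same model directly to frailty outcomes, with no teacher, gives practically the same odds ratios. The figures show what any clinical-only model does when a cause is omitted. They do not measure a defect peculiar to this framework.

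**A journal article condenses.** Network detail may be left to the full protocol. The point here is different: the article states the student's inputs and objective and claims interpretability and credibility from causal displays, and the stated objective does not carry that claim to the deployed model.

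**Limits are acknowledged.** The Discussion says that geriatric information inferred from laboratory data still needs to be validated, and decisions stay with physicians. Neither statement addresses causal structure.

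**Conclusion.** The point holds in limited form. As written, the article gives no basis for a causal reading of the student's attributions or of suggestions derived from them. The planned performance metrics cannot expose this, because they assess prediction only.

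The conclusion assumes that some geriatric factors affect both clinical markers and frailty. Where a marker instead acts on frailty through a geriatric factor, its weight in the student may reflect a real total effect. The article does not give these directions. The full-index causal structure is taken at face value here, and whether it is itself valid is a separate question.

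No figure in the article is wrong on this account, and the student's use as a predictor is not challenged. The odds ratios of about 1.3 to 1.9 illustrate a possible size under assumed correlations. They do not estimate what will occur in this cohort.

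**What to change.** 1. In Validation and evaluation and in Statistical plan, assign causal-effect visualization, do-calculus and counterfactual simulation to the full-index model.
2. Label the student's SHAP output as predictive association, in the article and on the dashboard.
3. State whether the intervention suggestions rest on full-index causal estimates or on the student's attributions, and reconcile the causal-learning and deployment sections accordingly.
4. In held-out patients with both index sets, report the agreement (for example, rank agreement) between teacher and student attributions for the shared clinical indices. The six partner centers contribute prospective data with geriatric assessment, so they can supply these patients. Present this as a descriptive check and not as proof of causal validity.

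Learning a separate mask from clinical indices alone should not be offered as a route to a causal reading, because it leaves the same factors unmeasured.

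The cost is a few sentences and one analysis of data already planned. The downside is a more modest claim for the deployed tool.
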